##### Control Procedures

For testing visits 3, 4, and 5, participants will arrive at the laboratory between 7 AM and 8 AM following an overnight fast and with abstinence from exercise or reduced general activity (ie, heavy to moderate activities of daily living) in the preceding 24 hours and for all follow-up sessions. These sampling procedures will be followed at all visits to account for circadian or diurnal rhythms [76]. Participants may be requested to abstain from particular medications (eg, aspirin), as advised by the medical doctor, if electing for a muscle biopsy.

To assist with adherence to study protocols, participants will be monitored via regular communication with the study coordinator on the days preceding each study visit. As a general consideration for participation in this study, participants will be encouraged not to alter their current physical activity levels, exercise habits, or dietary intakes for the entirety of the study. Participants are asked to report whether there have been any alterations in medications throughout the study, as we request that all medication interventions are stable for at least more than three months.

##### Biospecimen Sampling Protocols

On arrival and following supine rest (approximately 15 minutes), a cannula will be inserted into the antecubital vein, and a baseline (resting) blood sample (40 mL; biopsy, if consented) will be obtained. These baseline (resting) samples will be obtained on the first visit only, serving as the baseline for all other visits thereafter. Four additional blood samples following the 30-minute acute intervention will be collected immediately after the intervention (0-minute time point) and at 30, 60, and 120 minutes postintervention (total of 100 mL) to observe changes in tOC, ucOC, COP, and other measures. If elected, a postintervention biopsy will be conducted at the 60 minutes time point. At all time points, blood samples will be collected into EDTA and serum-separating tubes vacutainers for the appropriate collection of serum or plasma. Following 10-minute clotting time, samples will be centrifuged for 10 minutes at 4° C and immediately transferred to long-term storage at −80° C in 2 mL aliquots for later analysis.

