#### Randomization

Following baseline assessments, participants will be randomized into the acute intervention to explore the characteristics of older adults (by sex) with low or high muscle function (Figure 1). Participants will be randomized individually by a researcher external to this project (they will have no contact with the participants before or during the trial). This person will also have no intellectual or personal investment in the study design, data collection, or outcome. The order of the 3 conditions for each participant (AER, RE, or control) will be randomized using a sealed envelope method (block allocation) to prevent carryover effects between conditions. The envelopes will be stored separately in a locked cabinet, and each envelope will contain 3 pieces of paper that will state “AER,” “RE,” and “CON.” These pieces of paper will be folded to reduce their transparency.

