#### Study Intervention

##### Acute Intervention

Participants will complete the acute intervention (visit 3, 4, and 5) up to 14 days after completing the screening assessments and will complete the AER, RE, and CON conditions (Textbox 2) in a randomized order (described below). These visits will include blood sampling and optional skeletal muscle biopsies. Participants can elect to have none, 1 (at rest, for a baseline measure), or 4 biopsies (1 at rest for baseline and 1 following each condition). Each testing visit is approximately 3 hours in duration, including the 30-minute intervention (exercise or rest), and visits will be performed approximately 7 days apart, accounting for washout.

Acute intervention.

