#### Outcome Measures

##### Primary Outcomes

The primary outcome for this study is the peak change in circulating levels of ucOC from baseline compared with postacute exercise blood sampling time points (0, 30, 60, and 120 minutes) following the 3 acute interventions (AER, RE, and CON) between the low muscle function and high muscle function groups.

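### One resting ucOC sample, taken at the first acute visit, is the baseline for all three sessions, so two of three change scores span about 7 or 14 days

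*Protocol article*

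**What the plan says.** The Acute Intervention section has each participant attend visits 3, 4 and 5; participants "will complete the AER, RE, and CON conditions (Textbox 2) in a randomized order". It adds that "visits will be performed approximately 7 days apart, accounting for washout".

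The Biospecimen Sampling Protocols section describes a resting blood sample (and a biopsy, if consented) after cannulation, and then states: "These baseline (resting) samples will be obtained on the first visit only, serving as the baseline for all other visits thereafter". Post-session blood is "collected immediately after the intervention (0-minute time point) and at 30, 60, and 120 minutes postintervention". The biopsy option has the same structure: "4 biopsies (1 at rest for baseline and 1 following each condition").

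The Primary Outcomes section defines the endpoint as "the peak change in circulating levels of ucOC from baseline compared with postacute exercise blood sampling time points", for all three conditions, compared between the low and high muscle function groups. The statistical section plans baseline-versus-post comparisons at every post-session time.

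On carryover, the Randomization section says the order "will be randomized using a sealed envelope method (block allocation) to prevent carryover effects between conditions". No section describes a resting blood sample before the second or third session.

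**The concern.** The response of interest develops over 0 to 120 minutes. For the condition that falls first in a participant's order, change is measured against a sample from the same morning. For the other two it is measured against a sample from one or two weeks before. Those changes combine the acute response with whatever happened to resting ucOC in between: ordinary day-to-day variation, drift, or a residue of the previous session.

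Three things are at stake. The primary endpoint becomes noisier when the planned group difference is only 4%. A significant baseline-versus-post test in a later session cannot be credited to that session alone. And the washout is asserted without a pre-session level that could test it directly. Random order balances carryover across conditions but does not prevent it.

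**Working it through.** **Which change scores are affected.** There are three sessions and one baseline, with visits about 7 days apart. Session 1 has a same-day baseline. Session 2 uses one about 7 days old and session 3 one about 14 days old. That is 2 of 3 change scores per participant and, under balanced random order, two thirds of each condition's scores. This reads the first visit as the first acute visit, since the sentence stands in the acute-session sampling section. If it meant a screening visit, all three scores would lack a same-day baseline.

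**The plan's own figure.** Inputs from the statistical section: difference 4%, SD 6%, alpha 5%, 27 per group, 10% loss (54 − 5.4 = 48.6, about 24 per group). A two-sided two-sample t test (noncentral t) gives power 67% at 27 per group and 62% at 24. The stated power above 80% does not reproduce on this basis. That is a separate matter; 62% is used here only as the starting point.

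**Variance model.** Let s_w be the within-day SD of a single value and s_d the between-day SD of a person's resting level.

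- Same-day change: variance 2·s_w².
- Change against another day's baseline: 2·s_w² + 2·s_d².
- Ratio of the two: 1 + k², with k = s_d/s_w.
- Average for one condition under random order: 1 + (2/3)·k².

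The article gives no between-day SD, so k = 0.5, 1 and 2 is an assumed range. First take 6% as a same-day SD that is all within-day noise: 2·s_w² = 36, so s_w = 4.24% and s_d = 2.1%, 4.2% or 8.5%.

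| k | SD, later sessions | Power, later sessions only | SD, averaged over order | Power, averaged over order |
|---|---|---|---|---|
| 0 | 6.0% | 62% | 6.0% | 62% |
| 0.5 | √(36 × 1.25) = 6.7% | 52% | √(36 × 1.167) = 6.5% | 55% |
| 1 | √(36 × 2) = 8.5% | 36% | √(36 × 1.667) = 7.7% | 42% |
| 2 | √(36 × 5) = 13.4% | 17% | √(36 × 3.667) = 11.5% | 22% |

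Power is two-sided for 4% with 24 per group. The averaged columns describe a condition's change score as the design delivers it.

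**Sensitivity to what the 6% contains.** If half of the 36 is true difference in response between people, then 2·s_w² = 18. The averaged variances are 36 + 18·(2/3)·k² = 39, 48 and 84, with SDs of 6.2%, 6.9% and 9.2% and power of 58%, 50% and 32%. If the 6% already includes between-day variation, the single baseline costs nothing beyond what was planned.

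**What cancels.** With post-session value P and shared baseline B, (P_exercise − B) − (P_CON − B) = P_exercise − P_CON. An error in B drops out. On a percentage scale B remains only as the divisor. A visit effect common to both muscle-function groups also drops out of the between-group comparison.

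**What does not cancel.** P_exercise and P_CON come from different days, so their difference has noise variance 2·s_w² + 2·s_d², the same as a later-session change. The contrast removes the shared-baseline error but not the between-day noise.

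**The case against.** The best defence is that the design has its own control. A rest session is included in random order, the ANOVA crosses exercise type with time point, and the primary contrast is between groups. Baseline error therefore cancels where it matters most. Fixed morning arrival, overnight fasting, 24 hours without exercise, and requests for stable diet, activity and medication (Control Procedures section) all reduce day-to-day variation. This stands. It makes the problem mainly one of noise, and it leaves the within-condition baseline-versus-post tests as the most exposed part of the analysis.

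A reader might infer that effects in the later sessions cannot be attributed to exercise at all. The document does not support that, because the control session gives a valid comparison. A reader might also infer that carryover is invisible. That too goes too far: control-session values grouped by preceding condition, or period terms, give indirect evidence, though weak. Nor does anything in the document show that the first acute visit was unusual; the effect of a first cannulation, an optional biopsy or earlier screening tests is conjecture.

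The power loss is also open to challenge. It depends on an unstated between-day SD and on reading 6% as same-day noise, and later-session figures taken alone overstate it. Those points are accepted, which is why the averaged figures and both weaker readings of the 6% are given. None of them supplies the missing pre-session sample.

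**Conclusion.** The point holds as a weakness in a stated design rule. Two of every three primary change scores, and the tests built on them, compare samples about 7 or 14 days apart. Within-session change in those sessions is hard to attribute to the session alone, and the washout has no direct check.

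The main consequence is extra noise. Bias in the primary group contrast would need drift or carryover that differs between the muscle-function groups. The hypothesis of a larger ucOC rise in the low-function group makes differential carryover conceivable if a response persisted for a week, but nothing in the article shows that it does.

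Under the least favourable reading of the 6%, averaged power falls from 62% to between 55% and 22% over the assumed range. With half the variance as true heterogeneity it falls to between 58% and 32%. If 6% already covers between-day variation there is no further loss. The existence of the single baseline is certain; the size of its cost is not.

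**What to change.** **Remaining participants.** At visits 4 and 5, draw one resting serum tube before the intervention and use it as that session's baseline. Compare pre-session values by preceding condition as a direct check on carryover. With 38 of the planned 54 completed by 26 May 2019, this could reach at most 16 participants from that date.

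**All participants, including the 38.** Base the acute-effect conclusion on exercise minus control at the same post-session time points, compared between muscle-function groups, with a period term. Do not interpret later-session change from the first-visit sample as an acute effect by itself.

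**Keep the baselines apart.** Report results from session-specific baselines as a supporting analysis, so that two definitions of baseline are not pooled in the primary endpoint.

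**Cost.** Two extra tubes and ucOC assays per remaining participant, from a cannula that the post-session samples need anyway, plus an ethics amendment. The analysis change needs no new data. It does not recover the lost precision for participants already completed, because the control contrast still carries between-day noise.

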#### Outcome Measures

##### Primary Outcomes

The primary outcome for this study is the peak change in circulating levels of ucOC from baseline compared with postacute exercise blood sampling time points (0, 30, 60, and 120 minutes) following the 3 acute interventions (AER, RE, and CON) between the low muscle function and high muscle function groups.

##### Secondary Outcomes

The secondary outcomes for this study are (1) the difference in protein content related to atrophic and hypertrophic protein signaling at baseline between the low muscle function and high muscle function groups and (2) the difference in protein signaling (protein content) from baseline and compared with the postmuscle sampling timepoint (60 minutes) following the 3 acute interventions (AER, RE, and CON) between the low muscle function and high muscle function groups.

#### Data Collection and Analysis

##### Quantification of Osteocalcin

Serum tOC will be analyzed as described previously [9,10,19,39]. In brief, tOC will be measured using an automated immunoassay (Elecsys 170; Roche Diagnostics). Serum ucOC will be measured by the same immunoassay after absorption of cOC on 5 mg/mL hydroxyl-apatite slurry, following the method described by Gundberg et al [77].

##### Quantification of COP Cells

COP cell analysis will be performed as described previously [78,79]. In brief, peripheral blood samples (20 mL) will be collected (EDTA tubes) and processed for Ficoll-based gradient separation, and approximately 5×10^6^ peripheral blood mononuclear cells (PBMCs) will be obtained. Approximately 1×10^6^ PBMCs will be resuspended in fluorescence activated cell sorting (FACS) buffer, followed by a 10-minute blocking with fragment crystallizable receptor blocking reagent (BD Biosciences). Staining will then be performed with a viability marker (30 minutes), followed by washing (×2) with phosphate buffered saline (containing 5% fetal calf serum). Cells will be incubated with mouse antihuman CD45-Pacific Blue, CD3-PerCP, and CD19-APC (40 minutes). Staining of intracellular components will be permeabilized with Cytofix/Cytoperm (BD Biosciences) according to the manufacturer’s instructions, followed by incubation with mouse antihuman osteocalcin-phycoerytrhin at 4 °C (40 minutes), and then washed with Perm or wash buffer (×2).

##### Flow Cytometry

Cells will be analyzed using a BD FACS Canto II. FACS DiVa software will be used to analyze 50,000 total events for each sample and for the fluorescence minus one (FMO) controls. A total of 3 lasers and 8 different photomultiplier tube (PMT) channels will be used for the 6-color staining panel. Two FMOs will contain fluorochromes, except for the one to be controlled for. Compensation beads will be used to set the compensation controls for each fluorochrome. The PMT voltage values for fluorochromes will be set for each cell type based on the compensation controls. Doublet discrimination will be applied, and viability will be assessed by negative staining using the Live/Dead stain. Offline analysis will be performed using Flow Jo analytical software (Treestar).

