### Objectives

The primary objective of this study is to determine the change in circulating ucOC following acute exercise interventions between older adults with low and high muscle function (stratified based on leg muscle quality [LMQ]; see the *Lower Limb Maximal Strength and LMQ* section for the LMQ equation). To extend the current knowledge of ucOC in humans, and as an adjunct to this study, we will also perform in vitro experiments on cultured primary myotubes to uncover the mechanistic pathways of action of ucOC. In addition, as a secondary objective, we will aim to quantify the lineage of COP cells before and after exercise, as COP cells can potentially act as a regeneration and antiaging inducible factor and a precursor for osteocalcin.

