##### Gating Strategy

Cells will be gated for size, shape, and granularity using forward and side scatter parameters, as previously described by our group [78,79]. Briefly, serial gating steps will be applied to quantitate cellular populations. First, dead cells will be excluded, and then, a region will be set to encompass lymphocyte-, monocyte-, and granulocyte-enriched areas, followed by doublet discrimination, T cell (CD3) and B cell (CD19) elimination. For COP cells, after gating on live single mononuclear cells (on forward and side scatter plots), the CD45 and osteocalcin double positive cells will be calculated. Cutoff points to assign antigen positivity will be performed against matching FMO controls. The use of FMO significantly increases the sensitivity and specificity of analysis, as they effectively minimize the effect of nonspecific antibody binding and cell-specific autofluorescence. The gating quantification will be performed twice for the accurate quantification of the percentage of COP cells.

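### COP cell acquisition stops at 50,000 total events, nominally 5% of the cells stained, which gives up precision in a secondary objective if COP cells are rare

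*Protocol article*

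**What the plan says.** The Objectives section sets a secondary objective for COP cells: "we will aim to quantify the lineage of COP cells before and after exercise". Biospecimen Sampling Protocols lists COP among the measures followed over the four post-intervention time points. It takes the resting baseline at the first visit only, to serve all three conditions.

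Quantification of COP Cells describes the material: "approximately 5×10^6^ peripheral blood mononuclear cells (PBMCs) will be obtained", and then "Approximately 1×10^6^ PBMCs will be resuspended in fluorescence activated cell sorting (FACS) buffer". The Flow Cytometry section sets how much of it is read: "FACS DiVa software will be used to analyze 50,000 total events for each sample". Under Gating Strategy, dead cells, doublets, T cells and B cells are then removed, and the cells positive for both CD45 and osteocalcin are counted. The one step there aimed at precision is repetition of the gating: "The gating quantification will be performed twice for the accurate quantification of the percentage of COP cells".

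No section gives an expected COP frequency, a minimum number of COP events, or an effect size or SD for COP.

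**The concern.** The precision of a cell percentage depends on how many cells of the rare type are counted, not on how much blood was drawn or how many cells were stained. The 50,000 limit applies to all events, including those that gating later discards, so the number of COP cells behind each percentage could be small.

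The objective is a before/after contrast, so counting error enters from both samples. Because one baseline serves all three conditions, an imprecise baseline count carries into every change computed for that participant. Repeating the gating checks where the gates were placed. It draws no new cells and leaves the counting error as it was. What is at stake is the sharpness of the COP comparison, when most of the stained cells could have been read.

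**Working it through.** The article states no precision or power figure for COP, so there is none to reproduce. Its sample-size calculation concerns undercarboxylated osteocalcin (ucOC) only.

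**Inputs from the article**
- Events acquired per sample: 50,000 (Flow Cytometry).
- Cells stained: about 1,000,000, from about 5,000,000 obtained (Quantification of COP Cells).
- Participants: 27 per muscle-function group with 10% loss (Statistical Analysis and Determination of Sample Size), so 27 × 0.9 = 24.3, taken as 24.

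**Assumed input**
- COP share of total events, f. It is not given, so a range from 0.1% to 5% is shown.

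**Fractions read**
- 50,000 / 1,000,000 = 5% of the cells stained.
- 50,000 / 5,000,000 = 1% of the cells obtained.

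**Formulas (counting error only)**
- COP events: k = 50,000 × f.
- CV of one sample: √((1 − f)/k).
- CV of one participant's pre/post change: √2 × the one-sample CV, from two independent counts.
- SE of a group mean change: the change CV / √24.
- SE of a difference between two groups: the change CV × √(2/24).

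Example at f = 0.5%: k = 250; √(0.995/250) = 6.3%; × √2 = 8.9%; / √24 = 1.8%; 8.9% × √(2/24) = 2.6%.

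| Assumed f | COP events | CV, one sample | CV, one participant's change | SE, group mean change | SE, group difference | Change CV at 500,000 events |
|---|---|---|---|---|---|---|
| 0.1% | 50 | 14.1% | 20.0% | 4.1% | 5.8% | 6.3% |
| 0.5% | 250 | 6.3% | 8.9% | 1.8% | 2.6% | 2.8% |
| 1% | 500 | 4.4% | 6.3% | 1.3% | 1.8% | 2.0% |
| 2% | 1,000 | 3.1% | 4.4% | 0.9% | 1.3% | 1.4% |
| 5% | 2,500 | 1.9% | 2.8% | 0.6% | 0.8% | 0.9% |

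The last column divides the change CV by √10 = 3.2, since ten times as many events are counted. That ratio is the same at every f. Reading all 1,000,000 stained cells would give a factor of √20 = 4.5.

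**The case against.** Several counterarguments carry weight.

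- **Frequency.** The size of the problem rests on a COP frequency that the article does not give. The methods are described in brief, with reference to the group's earlier work, where the frequency may be known and the 50,000 limit may have been judged sufficient. At 2% to 5% of events the counting error is small. This stands, and is why only a range can be given.
- **Averaging.** The noise is random and averages down over participants. It enters the error term and does not create an exercise effect beyond the nominal type I error. Biological and assay variation in COP may be larger, and the article gives no SD for it. This also stands.
- **Standing of the measure.** COP is a secondary objective, but it is not among the two listed secondary outcomes, and no power claim is made for it. This limits the seriousness.
- **Spare material.** The 5% is nominal. Wash steps lose cells, and the controls may also need some, so not every unread cell is available.

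A reader might infer that counting noise is as large as the exercise effect the trial plans to detect. The article does not support that. It plans no COP effect. The 9% in the sample-size section is a previously reported change in ucOC, a serum protein. Even borrowed for scale, 9% is reached for a single participant only with about 2/0.09² = 247 COP events or fewer, which is about 0.5% of 50,000.

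A reader might also suspect that the blood draws are too small for the 20 mL the COP assay uses. The sampling section describes four further samples, the last three taken "at 30, 60, and 120 minutes postintervention (total of 100 mL) to observe changes in tOC, ucOC, COP, and other measures". Its plain reading is 100/4 = 25 mL each, which covers the 20 mL.

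**Conclusion.** The point holds as an avoidable loss of precision in a secondary objective. Three parts do not depend on any assumption: the limit is set on total events before exclusions, it reads nominally 5% of the stained cells, and repeated gating does not reduce counting error. The size depends on the assumed COP frequency. The loss is material if COP cells are below about 1% of total events, where one participant's change carries a counting CV above about 6%, and minor above that. The 1% mark is a judgement, not a figure from the article. The calculation treats cells as counted independently and covers counting error only. It shows no bias in the COP percentage, and it does not touch the primary ucOC outcome.

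**What to change.** In the Flow Cytometry section, replace the 50,000-event stop for the remaining samples. Either acquire as much of the stained tube as is recovered, for example with a target of 500,000 total events, or stop on a minimum number of gated COP events, or at the end of the tube if that comes first. The minimum follows from the wanted one-sample CV as about 1/CV². For illustration, 5% needs 1/0.05² = 400 COP events.

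For all samples, including those already recorded at 50,000 events, report the COP event count beside each percentage, and weight or flag low-count samples in the analysis.

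The cost is probably a few more minutes of cytometer time per tube and larger files (an estimate, not from the article), with no additional blood. The benefit is limited: the Results section reports 38 participants completed by 26 May 2019, so at most 54 − 38 = 16 of the planned 54, or 30%, could still gain. Later samples would be more precise than earlier ones, which the weighting is meant to handle.
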